## Background

The rates of recorded obstetric anal sphincter injuries (OASI) among primiparous women have tripled in the English National Health Service (NHS) from 1.8% in 2000 to 5.9% by 2011, with 70,000 women being affected during this period [1]. An OASI is defined as any degree of injury to the anal sphincter muscle sustained during childbirth. Short-term consequences of OASI include pain, bleeding and infection, which can result in urinary retention and constipation [2]. Long-term consequences include urinary and faecal incontinence, chronic pain and painful intercourse. Such morbidities can have a severe psychosocial impact and affect future birth choices [3]. Furthermore, there are significant cost implications for the NHS associated with further treatment and negligence claims relating to OASI between 2000 and 2010 are estimated to total £31.2 million [4]. OASI rates are also increasing in several countries including Australia, China and Canada [5–7]. Such trends render OASI prevention a quality improvement priority for maternity units across the world.

The aetiology of OASI is multifaceted and known risk factors include; birthweight greater than 4 kg, persistent occipito-posterior position, primiparity, induction of labour, prolonged second stage and an instrumental (assisted) birth [8, 9]. Research has shown that training gaps amongst midwives and obstetricians and a lack of awareness of risk factors may contribute to the increase in OASI rates [10–16]. Variations in practice, with increasing use of a “hands-poised” approach to protecting the perineum during childbirth as opposed to a “hands-on” approach are also thought to be contributing factors [1]. Not all perineal injuries are preventable, however, evidence from Scandinavia and small-scale studies in England show that OASI rates can be significantly reduced [10, 11, 17–19]. For instance, in Norway, the OASI rate decreased from 4.0 to 1.9% after the introduction of a package of interventions [10].

In light of the rising trends in OASI rates in England, a team of national experts met to discuss strategies to reverse this trend. There was unanimous agreement that there was potential for a ‘care bundle’ of evidence-based actions to be developed. A joint statement supporting this work was produced by the Royal College of Obstetricians and Gynaecologists (RCOG) and the Royal College of Midwives (RCM) [20].

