#### Data source

Patient-level data will be extracted from local electronic MIS for 15 units in England, Wales and Scotland, and from the Scottish Morbidity Record 02 (SMR02) and Scottish Birth Record (SBR) for one unit in Scotland. MIS capture detailed demographic and clinical information related to maternity care and outcomes, with the data entered by midwives and support staff in the antenatal clinic or labour ward. Although the participating units use nine different systems and the data format could slightly differ, there is sufficient similarity between them to develop a single dataset for analysis. SMR02, submitted by maternity units to the Information Services Division Scotland since 1975, collects data for all women admitted as inpatients or day cases to Scottish maternity units [28]. This register is subjected to regular quality assurance checks and since the late 1970s has been more than 99% complete.

The pre-defined data specification for MIS, SMR02 and SBR includes perineal trauma, maternal characteristics (e.g. age, body mass index, parity) and intrapartum care (e.g. episiotomy, induction of labour, epidural use, shoulder dystocia and mode of birth). An 18-month extract of patient-level data (which will include a baseline, transition and implementation phase) will be extracted from the data sources. This will be obtained at the end of March or April 2018 depending on when the region began roll-out to ensure 18 months of data for all units. While data for a longer period for pre-rollout is available, we will follow the recommendation that primary analyses need to be based mainly on data from those exposed to the intervention or control while clusters are in both conditions, supplemented only by data from immediately before or after the roll-out period [29]. The dataset will not include any patient identifiable information. It will be transferred to and stored at a secure server, and only named individuals from the Project Team will have access to the dataset. All participating units have signed a Data Sharing Agreement with the RCOG, and all users of the data are obliged to fully comply with Data Protection Legislation.

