#### Data analysis

In stepped-wedge designs, power calculations need to take into account both the clustered nature of the design and the confounding effect of time [30]. The statistical power for the study was calculated using the “steppedwedge” command in STATA 14 [31]. The “steppedwedge” command, written by Hemming and Girling [32] and based on the approach proposed by Hussey and Hughes [33], allows for power and detectable-difference calculations for binary outcomes, following the specification of the number of clusters (units) at each step, the number of steps, the average cluster (unit) size, and the intra-cluster correlation coefficient (ICC, rho). In this study, the number of steps and the number of units per step are both four, totalling 16 units. Unit sizes (the number of vaginal deliveries in each participating unit) were available from national maternity statistics data for each country [28, 34, 35]. There were on average 304 vaginal births a month for each participating unit (with a range of 113–539) in 2014/2015, therefore the average cluster size was 912 vaginal deliveries per unit in a three-month period (duration of each step). The baseline OASI rate and the intra-cluster correlation (ICC, rho) were calculated from English maternity clinical indicators data for 2013/14 [36]. For the 13 participating English units, the OASI rate for all vaginal deliveries was 3.2% and the ICC was 0.0062 (CI:0.0018 to 0.0214). The statistical power of the study to detect a 25% reduction in OASI rate (from 3.2 to 2.4%) is 0.92. Under various scenarios (e.g. using lower confidence interval value for ICC, a cluster size of 700 or a baseline OASI rate of 2.8%), the statistical power remains over 80%.

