In stepped-wedge studies, the proportion of units exposed to the intervention gradually increases, meaning that unexposed observations will, on average, be from an earlier calendar time than exposed observations [30]. Furthermore, improved reporting and increased awareness of the care bundle over the period is likely to have an impact on the OASI rates [1]. Thus, calendar time is associated with both the exposure to the intervention and also the outcome, and is therefore a potential confounder. We will use logistic mixed effects regression to model the log odds of sustaining an OASI, with a fixed effect for each step and a random effect to account for clustering at the unit level [33, 37]. The model will include a linear secular trend and also adjust for risk factors for OASI (maternal age, BMI, ethnicity, mode of delivery, episiotomy, birthweight, prolonged labour, and shoulder dystocia) [1].

Additional analyses are planned subject to completeness and quality of data collected for monitoring purposes throughout the study, including data on care bundle compliance, either on a paper form or electronically. In addition, these summary measures of organisational readiness and trends in the uptake of the intervention (i.e. percentage of clinicians trained and compliance rate) may also be used to explore the impact of these organisational factors on clinical outcomes.

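### Parity is missing from the covariate list, although the protocol names primiparity as an OASI risk factor and already extracts parity

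*Protocol article*

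**What the plan says.** Three places in the protocol article bear on this.

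- **Background.** The known risk factors for OASI are given as "birthweight greater than 4 kg, persistent occipito-posterior position, primiparity, induction of labour, prolonged second stage and an instrumental (assisted) birth". The same section reports that recorded rates among primiparous women "have tripled in the English National Health Service (NHS) from 1.8% in 2000 to 5.9% by 2011".
- **Data source.** The pre-defined specification for every data source includes "maternal characteristics (e.g. age, body mass index, parity") alongside items on intrapartum care.
- **Data analysis.** The model has a fixed effect for each step, a random effect for unit and a linear secular trend. It adjusts for the OASI risk factors "maternal age, BMI, ethnicity, mode of delivery, episiotomy, birthweight, prolonged labour, and shoulder dystocia".

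The last list has eight items and is not worded as a set of examples, whereas the Data source list is. The Abstract also commits the regression to adjusting for differences in obstetric risk factors between women giving birth before and after implementation. No section explains why parity is left out.

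**The concern.** A stepped-wedge study with continuous recruitment compares different women in the control and intervention periods, so the adjustment set has to deal with differences in case mix. Parity is a natural member of that set. The article itself calls primiparity a risk factor, parity is settled before labour begins, and the bundle cannot alter it. Adjusting for it therefore cannot remove part of the effect being estimated.

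Parity also varies in this study, because eligibility and the power calculation concern all vaginal births. The citations suggest one possible explanation. The covariate list and the trend in primiparous women carry the same reference number. A list taken from an analysis restricted to primiparous women could not have contained parity. That is an inference from the citations, and nothing below depends on it.

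If the share of primiparous women changes within units as the bundle is introduced, part of that change will be read as an effect of the bundle. A rise in the share would hide benefit and a fall would mimic it. Adding parity only after the data are seen could look data-driven.

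**Working it through.** **Inputs from the article**

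- OASI rate in primiparous women, English NHS, by 2011: 5.9% (Background).
- All vaginal births, 13 participating English units, 2013/14: "the OASI rate for all vaginal deliveries was 3.2% and the ICC was 0.0062 (CI:0.0018 to 0.0214") (Data analysis).
- Target and power: "to detect a 25% reduction in OASI rate (from 3.2 to 2.4%) is 0.92". The target difference is 3.2 − 2.4 = 0.8 points.
- Cluster-period size: "the average cluster size was 912 vaginal deliveries per unit in a three-month period (duration of each step"). There are four steps of four units.

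**Assumption.** The article gives no primiparous share, multiparous OASI rate or parity risk ratio. The primiparous share *s* is therefore assumed, with 35–45% as the main range and 30–50% as the wider one.

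**Step 1. Reproduce the stated power.** I used the Hussey and Hughes variance with 16 units, 4 steps, 5 periods, 912 births per unit-period, ICC 0.0062, binomial variance 0.032 × 0.968 and two-sided alpha 0.05 (assumed, not stated). The standard error of the effect is 0.2345 points. Power = Φ(0.8/0.2345 − 1.96) = Φ(1.45) = 0.927, against the stated 0.92. The parity point does not depend on this figure. It only calibrates step 5.

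**Step 2. What the two rates give without assumptions about *s*.** Primiparous versus all births: 5.9/3.2 = 1.84. Primiparous women are part of the 3.2%, so if the two rates are comparable, the ratio to multiparous women must exceed 1.84.

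**Step 3. Implied multiparous rate.** Solve 3.2 = 5.9*s* + *m*(1 − *s*), so *m* = (3.2 − 5.9*s*)/(1 − *s*).

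**Step 4. Effect of an assumed 2-point shift in primiparous share on the crude rate.** Movement = 0.02 × (5.9 − *m*), then divided by 0.8.

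| *s* (assumed) | *m* | Risk ratio 5.9/*m* | Risk difference (points) | Movement for 2-point shift (points) | Share of 0.8 |
|---|---|---|---|---|---|
| 30% | 2.04% | 2.9 | 3.86 | 0.077 | 10% |
| 35% | 1.75% | 3.4 | 4.15 | 0.083 | 10% |
| 40% | 1.40% | 4.2 | 4.50 | 0.090 | 11% |
| 45% | 0.99% | 6.0 | 4.91 | 0.098 | 12% |
| 50% | 0.50% | 11.8 | 5.40 | 0.108 | 14% |

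**Step 5. How large a chance shift would be.** Apply the model of step 1 to primiparous share, assuming the same ICC. The standard error scales with the binomial standard deviation:

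- *s* = 35%: 0.2345 × √(0.2275/0.030976) = 0.64 points.
- *s* = 45%: 0.2345 × √(0.2475/0.030976) = 0.66 points.

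A 2-point shift is thus about 3 standard errors. A shift of one standard error moves the crude OASI rate by 0.64 × 0.0415 = 0.026 to 0.66 × 0.0491 = 0.033 points, or 3–4% of the target. Using the ICC limits 0.0018 and 0.0214 changes this very little.

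**Step 6. Precision.** The share of outcome variance explained by parity is *s*(1 − *s*) × (risk difference)² / (0.032 × 0.968). At 35% this is 0.2275 × 0.0415²/0.030976 = 1.3%. At 45% it is 0.2475 × 0.0491²/0.030976 = 1.9%. Any gain is slight. In a logistic model a prognostic covariate does not in general shrink the standard error of the log odds ratio.

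**The case against.** The strongest reply is that the design already does most of the work. Every unit contributes control and intervention data. The unit effect largely absorbs stable differences in parity mix between units, and the step effects and trend absorb changes common to all units. Roll-out order was randomised by region, and routine records cover all births, so nothing described selects women by parity. This stands. A reader might infer that any difference in parity between periods or units passes straight into the estimate, and the model does not support that. Only a within-unit shift that coincides with roll-out does so, and the article points to no mechanism for one. Covariates related to parity, such as maternal age or mode of delivery, may also capture part of its effect.

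A reader might also infer that the article's own rates establish a three- to sixfold risk. They do not. That range is a risk ratio and requires an assumed primiparous share of about 31–45%. The two rates also differ in year and population. Nor does the article rank risk factors, so it does not show parity to be the strongest pre-labour predictor.

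Finally, the covariate list does not claim to repeat the Background list. It also omits induction and occipito-posterior position, and a condensed article may leave detail to the analysis plan. The first part is fair: this is an unexplained omission, not a strict contradiction. The second does not answer the point, because the article does state the list. An analysis plan that followed it would carry the omission forward, and one that added parity would depart from the published protocol.

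**Conclusion.** The point holds as an omission that should be corrected. The article names primiparity as a risk factor and specifies parity for extraction, then leaves it out of the stated adjustment set without a reason, in a study of all vaginal births.

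The size is moderate and rests on assumptions. Without an assumed primiparous share, the figures support only 1.84 for primiparous versus all births. Treating the two rates as comparable, a primiparous share of 35–45% gives a risk ratio against multiparous women of 3.4–6.0, and 30–50% gives 2.9–11.8. An assumed 2-point within-unit shift tied to roll-out would move the crude rate by 0.08–0.10 points (10–12% of the target) for shares of 35–45%. A chance shift of typical size would move it by about 0.03 points. Serious bias is possible but not shown. The case for the change is that parity is a relevant pre-labour variable, safe to adjust for and already available.

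**What to change.** In the Data analysis section, add parity (primiparous versus multiparous) to the covariates of the primary model, and carry the same list into the analysis plan before the outcome data are analysed. If parity was left out deliberately, state the reason there. A table of OASI rates by parity and phase would be a useful supplement, though the point does not depend on it.

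The cost is one further term in the model. Parity is already in the data specification, so there is no added data collection, and the stated sample size and power do not change. Any missing values can follow the multiple-imputation approach already described under Data management.

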### Data collection procedures to measure implementation outcomes

The study will prospectively measure the four implementation outcomes (acceptability, feasibility, coverage and sustainability) using quantitative and qualitative methods. Figure 4 brings together all the process metrics and indicates which implementation outcome they will assess and Fig. 5 illustrates the timing of data collection for each region.

**Fig. 4 Fig4:**
[figure not shown]
Data collection tools used to evaluate implementation outcomes. This brings together all the process metrics and indicates which implementation outcome they will assess

**Fig. 5 Fig5:**
[figure not shown]
Evaluation timeline outlining implementation components. This illustrates the timing of data collection for each region

#### Organisational change

The first stage of the evaluation will assess readiness for change within each unit. Weiner’s theory of organisational change will be used to measure organisational readiness and change efficacy [38]. This survey, completed by local champions as well as clinicians taking part in focus groups in their units, will assess whether the units have a supportive environment for quality improvement and learning.

#### Focus group discussions (FDGs)

Sixteen FDGs will be conducted with clinicians from participating units (one FDG per unit) during the transition phase. The FDGs will explore whether clinicians are receptive to change and willing to use the OASI Care Bundle as part of their routine practice. Participants will be recruited from clinicians working within the participating units and will comprise a mixture of midwives and obstetricians of varying experiences. Four FDGs will be also conducted with the local champions (one per implementing region) at the end of the transition phase in order to assess whether the care bundle is a locally appropriate intervention that does not interrupt practice.

Standard FDGs procedures will be followed – an experienced moderator will facilitate the session. The FDGs will explore 1) attitudes towards the care bundle, 2) experience of using the care bundle, 3) opinions of the skills development module, the practicalities of how training was rolled out and whether the ‘train the trainer’ model is appropriate, 4) views of the awareness campaign, 5) knowledge of the morbidity associated with perineal trauma, 6) perceptions of contextual factors (e.g. organisational culture, resources, leadership, support and motivational environment) which impact behavioural change interventions. An open-ended topic guide was developed by the evaluation team and clinical leads to facilitate discussion and ensure engagement, exploration and the opportunity for reflections on the care bundle. The information generated from the FGDs will be used to understand acceptability, feasibility, coverage and sustainability of the care bundle. The information will also provide an understanding of the barriers and enablers that are associated with implementing quality improvement within maternity units.

#### In-depth interviews with the local champions

We will conduct in-depth interviews with all of the primary champions at the end of the implementation period. This will mean a total of 32 interviews. The objective of these interviews will explore whether the care bundle has become part of routine practice and whether all elements are being used consistently. Additionally, these interviews will explore the challenges experienced during implementation of the care bundle, feelings of empowerment and support received from the professional organisations.

#### In-depth interviews with women

Current environment encourages informed choice and therefore women’s opinion must be included, where possible, in order to facilitate this. It is suggested that a ‘hands-on’ approach restricts women’s choices and affects their birthing position [39]. A missing element in this continued debate is discussion with women and this is essential to inform evidence-based practice. As mobility in labour and perceptions of pain will be explored during the interviews, for women to be eligible to take part in the interviews, they must have had a vaginal birth without an epidural, or spinal anaesthesia and received the OASI Care Bundle as part of their care. The attending midwife will provide eligible women with information about the interviews and if the woman is interested in taking part, she will be contacted by a member of the OASI Project Team at a convenient time in order to conduct a telephone interview. A proportionate approach to consent will be taken, i.e. by providing contact details and agreeing to a time for the interview, the woman has consented to participating. Women who take part in the interviews are given assurances that everything they say is anonymous, that they are free to withdraw at any time and that taking part will not affect the care that they, or their baby receives. A total of forty-eight interviews will be conducted (three per participating unit). The interviews will explore the woman’s birth story, in particular memories of pain, mobility during labour, birthing position and any guidance that was received during childbirth.

#### Monitoring of clinical data during implementation of the OASI care bundle

Clinical data will be monitored on a weekly basis by the evaluation team. These data include rates of OASI, episiotomy and caesarean sections, as well as the number of eligible and care bundle compliant births. In addition to providing information on coverage, routine monitoring of data may be used to trigger additional Project Team communication or support if an unusual clinical activity is observed. Additionally, evidence of integration of the care bundle into routine practice will be continuously monitored by assessing the number of eligible and care bundle compliant births each week. Statistical process control techniques will identify any unusual patterns in OASI or compliance rates.

Each unit will be sent a six month summary of their OASI rates and compliance data. In order to facilitate shared learning, this six month summary will also be aggregated by region (with anonymization of data) and be provided to the four units within that region. This is a quality improvement project which aims to reduce rates of OASI. With this in mind, a critical review after six months, with sharing of anonymised results amongst neighbouring units, will facilitate learning for all units in order to understand what has gone well and which areas need to be targeted to further accelerate any change in OASI rates. Similar summaries (to individual units and at regional level) will be provided at nine months and twelve months. Provision of such feedback contributes to the ‘Communications and Awareness Campaign’ component of the ‘Theory of Change’ and will provide information about the effectiveness of the care bundle. Such information will promote engagement with the care bundle and help enable change.

Fidelity is seen as a crucial factor to determine whether the care bundle is implemented as it is intended. However, as the care bundle is implemented at time of birth, it is not possible in practice for an impartial observer to monitor whether each care bundle component is correctly carried out for each birth. Where possible, the Project Team advocates the presence of a second midwife at birth who can observe practice and help identify any training needs. Additionally, the awareness campaign, continued skills development, presence of the local champions and unit visits by the Project Team will contribute to ensuring that intervention is correctly implemented.

An independent Advisory Group containing professional stakeholders with relevant expertise in perineal trauma and quality improvement was established. The Advisory Group also contains lay representation to ensure that woman-centred care remains at the fore-front. The Advisory Group provides an independent oversight of project activities and meets with the Project Team every six months.

